### Standardization and auditory conditions

3.6

All auditory recordings are presented using standardized voice characteristics to minimize variability unrelated to the experimental manipulation. The same speaker’s voice and recording quality are used across all conditions. All auditory stimuli are approximately equal in duration (10 min), presented as spoken audio, and matched in general recording format. They differ primarily in their regulatory content and instructions.

The intervention duration was set to approximately 10 min for both mindfulness and relaxation exercises to align with prior work on brief mind–body interventions and to remain feasible in the MEG environment. Single short-session mindfulness interventions have been shown to affect state mindfulness, perceived stress, attention, and affect, and recent evidence suggests that 10-min and 20-min mindfulness meditations may produce comparable improvements in state mindfulness, supporting the use of a 10-min format to assess short-term state effects while minimizing participant burden (Ueberholz and Fiocco, 2022; Palmer et al., 2023; Luberto et al., 2020).

#### Mindfulness condition (body scan)

3.6.1

The mindfulness condition consists of a guided body scan exercise based on standardized mindfulness material. Participants are guided to systematically direct attention to different body regions and to observe bodily sensations in a present-focused and non-judgmental manner. The exercise encourages participants to notice bodily sensations without attempting to change them and to gently return attention to the body when distracted. This condition is intended to target interoceptive awareness, attentional regulation, and present-centered awareness.

#### Relaxation condition (safe place imagery)

3.6.2

The relaxation condition consists of a guided safe place imagery exercise adapted from Reddemann’s safe place procedure. Participants are instructed to imagine a personally meaningful place where they can feel safe, protected, and comfortable. Narration encourages the use of multiple sensory modalities, including visual, auditory, tactile, and emotional imagery, to increase the vividness of the imagined place. This condition is intended to support relaxation, emotional safety, and imagery-based affect regulation.

#### Control condition (podcast)

3.6.3

The control condition consists of a spoken informational podcast presented in a calm, conversational voice. The selected segment discusses a general-interest scientific topic and is intended to provide coherent spoken input without guiding participants toward mindfulness, relaxation, imagery, breathing, or emotional regulation. The podcast therefore serves as a non-regulatory auditory control condition rather than an intervention condition. The podcast condition is matched to the mindfulness body scan and relaxation guided imagery conditions in duration, auditory modality, and general speech characteristics, including continuous spoken language, similar pacing, and speaker characteristics, while differing specifically in the absence of explicit regulatory instructions. This allows speech-related neural responses to be assessed across conditions using comparable spoken input without an explicit mindfulness, imagery, breathing, or relaxation component. The control condition therefore accounts for non-specific effects associated with listening to spoken audio, including auditory stimulation, sustained attention, and language processing, while focusing the comparison on intervention-specific regulatory processes such as attentional focus, interoceptive awareness, or imagery-based modulation.

The use of structurally matched audio conditions as controls is consistent with experimental designs in mindfulness and relaxation research, where non-regulatory spoken material, such as documentary or general-interest content, is used to control for sensory and attentional engagement without inducing targeted regulation processes (Palmer et al., 2023; Vieth and von Stockhausen, 2022; Yang et al., 2022).

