### Why speech matters for neuroscience-based psychotherapy

1.6

Psychotherapy is fundamentally language-based. Verbal communication is not only a medium through which therapeutic interventions are delivered, but also a channel through which individuals express, organize, and reflect on internal states. In the present paradigm, spoken language is also the common delivery format of all auditory conditions. The body scan, safe place imagery, and podcast control condition are all presented as spoken audio, which means that neural responses to heard speech are an inherent part of the experimental setting. Because MEG can capture neural dynamics related to auditory speech processing with high temporal precision, speech-related neural tracking provides a relevant stimulus-engagement measure within this design. In the context of mind–body interventions, speech may provide an additional window into how participants process regulatory instructions and describe their subjective experience after regulation. At the same time, speech-related measures are methodologically challenging in MEG because overt speech can introduce movement and muscle artifacts. For this reason, speech is included in the present protocol as a complementary and carefully constrained extension of the main brain–body paradigm, rather than as the central focus of the study (Abbasi et al., 2021; Sanders, 2010). Because the podcast condition primarily requires sustained engagement with externally presented speech, whereas the body scan and safe place imagery conditions use speech to guide internally oriented regulatory processes, TRF-based neural speech tracking is expected to provide an index of stimulus engagement that may be strongest in the podcast condition.

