#### Primary

2.3.1

Preregistered hypotheses focus on differences between the conditions in (a) subjective stress and relaxation ratings, (b) HR, HRV (RMSSD), and respiration rate, and (c) global-band MEG power (theta, alpha, beta).

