#### Secondary

2.3.2

TRF-based neural speech tracking is included as a preregistered stimulus-engagement measure: TRF-based speech tracking is expected to be stronger in the control/podcast condition than in the mindfulness/body scan and relaxation/safe place imagery conditions. This expectation is based on the rationale that the podcast condition primarily requires sustained engagement with externally presented speech, whereas the body scan and safe place imagery conditions use spoken guidance to support internally oriented regulatory processes such as interoceptive attention, bodily awareness, or mental imagery.

Brain–body coupling outcomes are treated as preregistered non-directional mechanistic outcomes, whereas autonomic coupling extensions, time-resolved coupling extensions, speech-production features, and psychological or lifestyle correlates are treated as exploratory unless explicitly specified otherwise in the preregistration.

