### Statistical analysis plan (overview)

3.9

Condition will be modeled as a within-subject factor with three levels: mindfulness/body scan, relaxation/safe place imagery, and control/podcast. The choice of statistical procedure will depend on the structure and distribution of the measures derived, for example multilevel models, parametric tests, or non-parametric tests. Repeated-measures ANOVA will be used for complete within-subject datasets when model assumptions are sufficiently met. Linear mixed-effects models will be used when appropriate to account for incomplete condition-level data, unequal numbers of usable observations, participant-level variability, or additional covariates such as condition order or medication status. If substantial deviations from model assumptions occur, for example due to pronounced non-normality, influential outliers, or distributional characteristics that are not adequately addressed by standard corrections or transformations, robust or non-parametric sensitivity analyses may be considered and explicitly reported.

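### The podcast is said to account for sustained attention and language processing, yet the plan predicts stronger speech engagement in the podcast, so active-versus-podcast band-power differences cannot be attributed to regulation alone

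*Protocol article*

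**What the plan says.** Section 3.6.3 of the protocol article describes the podcast as matched to both exercises in duration, modality and general speech characteristics, "while differing specifically in the absence of explicit regulatory instructions". From this it concludes: "The control condition therefore accounts for non-specific effects associated with listening to spoken audio, including auditory stimulation, sustained attention, and language processing". The sentence goes on: "while focusing the comparison on intervention-specific regulatory processes such as attentional focus, interoceptive awareness, or imagery-based modulation". The next paragraph supports the choice by pointing to other studies that use neutral spoken material to equalise sensory and attentional engagement.

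Section 2.3.2 gives a directional preregistered hypothesis: "TRF-based speech tracking is expected to be stronger in the control/podcast condition than in the mindfulness/body scan and relaxation/safe place imagery conditions". The reason, given there and in section 1.6, is that "the podcast condition primarily requires sustained engagement with externally presented speech", whereas the two exercises use speech to turn attention inward. Section 1.6 words the expectation more softly and calls tracking "an index of stimulus engagement that may be strongest in the podcast condition".

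The primary hypotheses in section 2.3.1 include condition differences in "global-band MEG power (theta, alpha, beta"), and section 3.7.7 averages band power across sensors for the global analysis. For mixed models, section 3.9 gives as examples "additional covariates such as condition order or medication status". Section 3.9.1 treats TRF tracking as an outcome of its own.

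**The concern.** One section credits the podcast with dealing with attention to speech and language processing. Another predicts that the plan's engagement measure will differ between the podcast and both exercises, because of what the podcast asks of the listener. The plan does not say how the second statement qualifies the first.

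What is at stake is the interpretation of a primary outcome. A reader who relies on section 3.6.3 would take a band-power difference against the podcast as a sign of regulation. If the tracking hypothesis is confirmed, the same study will have shown that the conditions also differ in engagement with the heard speech. No section carries that result into the reading of the band-power contrasts. The limitations in section 4.3 name recovery, habituation, fatigue and carryover, but not unequal engagement.

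**Working it through.** The plan states no figure on this point, so there is nothing to reproduce. The check sets the statements side by side and asks what each contrast can identify.

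**Step 1: the contrasts.** Three conditions give three pairwise contrasts: body scan minus podcast, safe place minus podcast, and body scan minus safe place. Two of the three involve the podcast.

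**Step 2: what each contains.** As a simplification, write a band-power difference from the podcast as E + R. E is the part due to different engagement with the heard speech, and R is the part due to regulation.

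- Body scan minus podcast = E(body scan) + R(body scan)
- Safe place minus podcast = E(safe place) + R(safe place)
- Body scan minus safe place = [E(body scan) − E(safe place)] + [R(body scan) − R(safe place)]

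**Step 3: apply the two statements.** Reading a podcast contrast as regulation, as section 3.6.3 invites, needs E = 0 in the first two lines. Section 2.3.2 predicts that engagement is lower in both exercises than in the podcast. That prediction concerns tracking, not band power, so it does not prove that E differs from zero. It does remove the plan's ground for taking E as zero. Each podcast contrast then gives one estimate for two unknown parts. For the third line, the plan predicts no tracking difference between the two exercises, so the prediction gives no reason to doubt that contrast.

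**Step 4: does the plan separate E from R elsewhere?** Global power is averaged across sensors (3.7.7), so sensors over auditory regions contribute. The covariates given as examples in 3.9 do not include engagement. Regional analyses, including a temporal/auditory region, are foreseen in 3.7.2 as exploratory and are not tied to this question. Multiplicity correction (3.9.3) limits chance findings and does not bear on what a contrast measures.

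**Step 5: illustration only.** Suppose R = 0 and E shifts band power by a standardised paired difference dz. The documents give no value for dz, and N = 30 rests on feasibility (3.4.2.1). The power of a two-sided paired t-test with 29 degrees of freedom follows from the noncentral t distribution with noncentrality dz × √30:

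| Assumed dz | alpha 0.05 | alpha 0.05/3 |
|---|---|---|
| 0.2 | 18.5% | 8.9% |
| 0.3 | 35.5% | 20.3% |
| 0.5 | 75.4% | 58.3% |
| 0.8 | 98.8% | 96.1% |

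These figures are ordinary power to detect a real condition difference of assumed size, for one test without the omnibus step that section 3.9.3 requires first. They are not false-positive rates. They show only that a moderate engagement effect could reach significance at this sample size.

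**The case against.** The strongest reply is that inward attention is part of the intervention. Section 3.6.3 lists attentional focus among the processes that the contrast should show, section 1.4 describes mindfulness as attentional regulation, and section 3.6.1 names it as a target of the body scan. The predicted drop in tracking may then be a consequence of the mechanism and not a rival to it. All three conditions also share about 10 minutes of listening to the same voice, and common listening demands can coexist with a different direction of attention. Much of this stands. It rules out calling the engagement difference a pure confounder. It does not rescue the statement that sustained attention and language processing are accounted for, because the same sentence puts one kind of attention on the controlled side and another on the regulatory side without saying where the line runs.

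A second reply is that section 4.4 limits interpretation to mechanistic and descriptive statements, and that TRF tracking will be reported by condition in any case. Both are true and lower the stakes. But mechanistic attribution is exactly what is in doubt, and reporting the two results separately does not tell the reader to read them together.

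A reader might go further and infer that the podcast contrasts say nothing about regulation, or that the plan inflates its type I error. The documents support neither. The randomised difference between conditions remains estimable, regulation may be part of it, and a real difference that is detected is not a false positive.

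**Conclusion.** The concern holds in a limited form. Sections 3.6.3 and 2.3.2 do not fit together on engagement with speech. If the tracking hypothesis is confirmed, active-versus-podcast differences in global band power cannot be attributed to regulation alone. They may reflect less outward speech engagement, regulation, or both.

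The reach is two of three pairwise contrasts on one of the three primary outcome domains. The argument is not made here for the subjective ratings or for the cardiac and respiratory outcomes. Body scan versus safe place, which addresses the primary research question in section 2.2, is not affected by this prediction. The podcast still controls for modality, stimulation, duration and voice. No size can be put on the engagement share from the documents.

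The conclusion rests on two assumptions: that TRF tracking indexes engagement, as the plan says, and that engagement with speech can affect band power, which the plan neither asserts nor excludes.

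**What to change.** - In section 3.6.3, limit the control claim to auditory modality, stimulation, duration and voice. Remove the statement that sustained attention and language processing are accounted for.
- State before results are seen that an active-versus-podcast difference in band power is the total effect of guided inward practice versus outward listening, and report it beside the TRF tracking difference for the same pair of conditions.
- Name unequal speech engagement as a limitation in section 4.3.

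Repeating the contrast without the temporal/auditory region is at most an optional partial check, since attention effects need not be confined there.

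Three apparent remedies should be avoided. TRF tracking should not enter as an adjustment covariate, because it is measured after condition onset and may lie on the intervention's pathway. The resting baseline is a poor comparator, because it has a fixed position after the stressor and is confounded with time and recovery. Confining all regulation wording to body scan versus safe place would give up the only non-regulatory reference and would still mix regulation with content.

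The required changes are to wording and reporting and need no new data. The price is that the podcast contrasts carry a narrower claim.

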### Measures

3.7

#### Data acquisition and synchronization

3.7.1

Neural, physiological, auditory, and behavioral data are acquired within a synchronized experimental setup. Auditory stimulus presentation, condition randomization, event timing, and trigger transmission to the magnetoencephalography (MEG) system are controlled using MATLAB, the Objective Psychophysics Toolbox, and Psychtoolbox 3 (Brainard, 1997; Pelli, 1997; Kleiner et al., 2007; Hartmann and Weisz, 2020). Brain activity is recorded in a magnetically shielded room using a 306-channel Elekta Neuromag TRIUX MEG system, comprising 102 magnetometers and 204 planar gradiometers. MEG data are sampled at 1000 Hz and filtered online between 0.1 and 330 Hz. Head position is monitored using five head-position indicator coils. Anatomical landmarks, including the nasion and left and right preauricular points, coil positions, and additional head-shape points are digitized using a Polhemus FASTRAK system. Recordings are processed with MaxFilter using signal space separation to reduce external noise and align recordings to a standard head position (Taulu et al., 2004; Taulu and Simola, 2006).

Physiological signals are recorded simultaneously using the MEG system’s built-in biochannels at 1000 Hz. Electrocardiography (ECG) is recorded using two electrodes placed on the right collarbone and the left side of the ribcage, with a ground electrode placed between the shoulder blades at neck height. Respiration is measured using a respiratory belt fastened around the abdomen. Electrooculography (EOG) is recorded using electrodes positioned above and below the right eye and at the outer canthi to support artifact identification. Auditory stimuli are presented through MEG-compatible in-ear headphones, and verbal responses are recorded using a microphone mounted inside the MEG room and documented in written form by the researcher.

#### Neural measures

3.7.2

Neural activity is recorded continuously using MEG to capture fast neural dynamics during the resting baseline and all auditory conditions following the stress induction. Neural outcomes include spectral power estimates in predefined frequency bands relevant to regulatory processes, including alpha (8–13 Hz), theta (4–7 Hz), and beta (13–30 Hz), summarized using predefined sensor-level summaries (e.g., global and region-of-interest averages). Exploratory analyses may additionally examine condition-related differences within predefined sensor- or source-level regions of interest (e.g., frontal/midline, temporal/auditory, parietal/posterior), depending on the specific analysis plan. In addition, TRF-based neural speech-tracking analyses will relate acoustic features of the auditory stimuli to MEG activity, providing an index of neural tracking of the spoken audio material.

#### Autonomic physiological measures

3.7.3

Cardiac activity (ECG) and respiration (respiratory belt) are recorded simultaneously with MEG to quantify autonomic regulation across the paradigm. Derived autonomic measures include heart rate variability (HRV; time-domain indices such as RMSSD), mean heart rate (HR; beats per minute), and respiration rate (RespRate; breaths per minute), calculated for each experimental phase/condition. The cardiac and respiratory time series may also support exploratory analyses of autonomic coupling, such as heart–breathing coordination across experimental conditions and provide the physiological basis for brain–body coupling analyses.

#### Brain–body interaction measures (brain–body coupling)

3.7.4

Brain–body coupling between MEG dynamics and autonomic physiology will be assessed using complementary approaches. First, coupling will be quantified using heartbeat-locked (R-peak-locked) MEG analyses and respiration-locked MEG analyses, in which MEG activity is time-locked to cardiac R-peaks and respiratory phase or peak events to derive condition-specific coupling indices (e.g., event-locked responses and/or oscillatory power changes around cardiac and respiratory cycles). Second, as an exploratory time-resolved extension, coupling will be examined using dynamic multivariate time-series approaches that integrate neural, cardiac, and respiratory time series. These approaches will be used to characterize lagged statistical dependencies between time-resolved MEG features (e.g., band-limited power envelopes in theta/alpha/beta, extracted per sensor or ROI) and cardiac/respiratory signals, while explicitly avoiding causal interpretation. The exact modeling approach will be selected based on data quality, model assumptions, and the temporal structure of the derived neural and physiological signals. Brain–body coupling analyses will be treated as preregistered, non-directional mechanistic analyses of condition-related differences. Exploratory extensions, including time-resolved coupling approaches, will be clearly labeled as such, and multiple-comparison control will be applied for high-dimensional neural outcomes where applicable.

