#### Preprocessing and data quality

3.7.7

MEG preprocessing will follow established procedures for continuous MEG data and will be implemented using Python-based analysis tools, including MNE-Python (Gramfort et al., 2013). Preprocessing will include signal-space-separation-based noise reduction, filtering between 0.1 and 40 Hz, identification and correction of ocular and cardiac artifacts using independent component analysis, resampling to 100 Hz, and segmentation of the continuous data into condition-specific analysis windows. Components related to cardiac and ocular activity will be identified using the simultaneously recorded ECG and EOG signals and inspected as part of quality control.

For spectral analyses, power spectra will be estimated using Welch’s method, a Fourier-based approach that provides a stable estimate of how signal power is distributed across frequencies (Welch, 1967). These will be summarized within the predefined frequency bands relevant to the preregistered hypotheses. These band-limited power estimates will be averaged across sensors for global analyses and, where applicable, summarized within predefined sensor-level or source-level regions of interest. For neural speech-tracking analyses, preprocessed MEG data will be aligned with the auditory stimulus material and prepared for temporal response function analyses.

Physiological preprocessing will be conducted on the temporally aligned ECG and respiration recordings using Python-based signal-processing tools, including NeuroKit2 (Makowski et al., 2021). ECG preprocessing will include signal cleaning, optional signal inversion where required, R-peak detection, artifact correction of detected peaks, and derivation of interbeat intervals. Heart rate will be calculated from the corrected R-peak series, and HRV will be quantified using time-domain measures, with RMSSD used as the primary HRV metric. Respiration preprocessing will include respiratory signal processing, detection of respiration peaks, and calculation of respiration rate. Physiological features will be extracted for each experimental condition and, where appropriate, additionally summarized in 30-s segments to support data-quality inspection.

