#### Exploratory and mechanistic analyses

3.9.1

Mechanistic and exploratory analyses will examine neural dynamics, autonomic coupling, brain–body coupling metrics, and speech-related variables. Exploratory autonomic coupling analyses may examine associations between cardiac and respiratory dynamics, such as temporal relationships between HR, HRV, and respiration, to characterize heart–breathing coordination across conditions. These analyses will be treated as exploratory and hypothesis-generating.

Brain–body coupling analyses will include heartbeat-locked (R-peak-locked) MEG analyses, respiration-locked MEG analyses, and exploratory time-resolved coupling approaches integrating MEG, cardiac, and respiratory signals. These analyses will be used to characterize statistical dependencies between time-resolved MEG features and autonomic physiology, without making causal claims.

TRF-based neural speech tracking will be analyzed as a preregistered stimulus-engagement measure. Speech-production analyses may focus on acoustic features of brief post-condition verbal responses, such as speech rate, pause characteristics, pitch/F0, and voice quality measures, depending on recording quality and the structure of the extracted speech data. Speech-production analyses will be explicitly labeled as exploratory and interpreted accordingly. These analyses will not be interpreted as primary tests of intervention efficacy.

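### The heartbeat- and respiration-locked coupling contrast has no stated control for event number or cycle length, so a heart- or breathing-rate change alone can appear as a coupling difference

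*Protocol article*

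**What the plan says.** Section 2.3.1 of the protocol article lists "HR, HRV (RMSSD), and respiration rate" among the primary outcomes hypothesised to differ between conditions. It gives neither direction nor size.

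Section 3.7.4 defines the coupling index: "MEG activity is time-locked to cardiac R-peaks and respiratory phase or peak events to derive condition-specific coupling indices". Its form is left open; the examples given are "event-locked responses and/or oscillatory power changes around cardiac and respiratory cycles". The status of the comparison is fixed: "Brain–body coupling analyses will be treated as preregistered, non-directional mechanistic analyses of condition-related differences". Section 3.9.1 repeats the plan: "Brain–body coupling analyses will include heartbeat-locked (R-peak-locked) MEG analyses, respiration-locked MEG analyses".

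The handling that comes nearest to the issue is:
- Section 3.9 allows mixed models with "additional covariates such as condition order or medication status". Heart rate and respiration rate are not named.
- Section 3.7.7 provides for "identification and correction of ocular and cardiac artifacts using independent component analysis".
- Section 3.7.1 describes head-position coils and MaxFilter with alignment to a standard head position.
- Sections 3.7.4 and 3.9.3 provide multiplicity control.

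None of these equalises event numbers, corrects for overlapping cycles or supplies a surrogate reference.

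**The concern.** Two parts of the plan meet here without being reconciled. If the primary autonomic hypotheses are right, the conditions differ in how many R-peaks and breaths a block contains and in how far apart they lie. An event-locked index can respond to both.

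- **Event count.** A non-negative index (response magnitude, phase locking, modulation depth) has a positive expectation even with no coupling, and that expectation grows as the number of events falls.
- **Overlap.** When cycles are shorter, activity belonging to the neighbouring beat or breath falls inside the analysis window. This alters the locked average even if the response to each event is identical, and it affects signed averages too.

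Section 1.5 presents brain–body coupling as the mechanistic core of the study, meant to add something beyond changes in cardiac activity or respiration. An index that moves with rate alone cannot show that addition. The secondary coupling result could restate the primary autonomic result and be read as a separate mechanism.

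**Working it through.** The article gives no effect size, power or expected rates for coupling, and its sample size rests on feasibility (3.4.2.1), so there is no figure of its own to reproduce. The check is whether rate alone can move the index, and by how much.

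**Inputs from the article:** blocks of about 10 min (3.5); N = 30 (3.4.2.1); two-sided 0.05 (3.9.3). **Assumed:** all heart and breathing rates, the same rates in every participant, all 30 participants usable, and a single uncorrected paired contrast.

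**1. Event count.** Events n = rate × 10. With no coupling, a phase-locking index (mean resultant length) has expectation √(π/(4n)) = 0.886/√n and variance (1 − π/4)/n.

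| Rates compared | Events | Null index | Ratio |
|---|---|---|---|
| 14 vs 12 breaths/min | 140 vs 120 | 0.0749 vs 0.0809 | 1.08 |
| 14 vs 10 breaths/min | 140 vs 100 | 0.0749 vs 0.0886 | 1.18 |
| 15 vs 10 breaths/min | 150 vs 100 | 0.0724 vs 0.0886 | 1.22 |
| 75 vs 70 beats/min | 750 vs 700 | 0.0324 vs 0.0335 | 1.04 |
| 75 vs 65 beats/min | 750 vs 650 | 0.0324 vs 0.0348 | 1.07 |

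**2. Effect on the test.** For 15 versus 10 breaths/min the spurious mean difference is 0.0163. The SD of the paired difference is √[(1 − π/4)(1/100 + 1/150)] = √(0.2146 × 0.01667) = 0.0598. The noncentrality is 0.0163 × √30 / 0.0598 = 1.49, which on 29 degrees of freedom gives a rejection probability of about 0.30. Simulation (4,000 runs per row, no coupling in either condition) agrees:

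| Rates compared | False-positive rate | With equal event counts |
|---|---|---|
| 14 vs 14 breaths/min | 0.051 | 0.046 |
| 14 vs 12 | 0.083 | 0.047 |
| 14 vs 10 | 0.217 | 0.048 |
| 15 vs 10 | 0.287 | 0.050 |
| 75 vs 75 beats/min | 0.048 | 0.049 |
| 75 vs 70 | 0.060 | 0.053 |
| 75 vs 65 | 0.086 | 0.056 |

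A separate simulation gave about 0.07, 0.21, 0.30 and 0.07 for 14 vs 12, 14 vs 10, 15 vs 10 and 75 vs 65. Subtracting the null expectation for each count also brought the rate back to about 0.05.

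**3. Overlap.** Here the response to every event was identical, there was no noise, and only the rate changed. The response shape is assumed.
- R-locked mean amplitude at 0.45–0.75 s: −0.366 at 60, −0.326 at 65 and −0.231 at 75 beats/min. From 65 to 75 the magnitude falls by (0.326 − 0.231)/0.326 = 29%.
- Respiration-peak-locked peak-to-trough: 1.00 at 10, 0.94 at 15 and 0.85 at 18 breaths/min.

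Equal counts cure the first route but not this one.

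**The case against.** **The preregistration may hold a control.** It is not shown, the article's analysis section is an overview, and the covariates are given only as examples. That stands as a limit: if a control is preregistered, one sentence in the article settles the matter. But the article itself fixes the locking events, the per-condition index and the contrast, and carrying out that contrast as stated can produce a false coupling difference. That is more than missing detail.

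**The index may not be biased by count.** This is correct in part. Signed average amplitudes or signed power changes carry no count bias, and locking to respiratory phase eases the cycle-length problem. A reader might infer that the slower-breathing condition will tend to show the larger coupling index under the plan as it stands. The article does not support that, because it leaves the index open; the inference holds for count bias only if a non-negative index is chosen. Overlap still affects signed averages.

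**The large figures need large rate gaps.** Also fair. No described condition paces breathing, and 15 to 10 breaths/min is a fall of one third. At smaller gaps the inflation is modest, and for the heart it is small throughout. The 22% is a ratio of noise floors. With a true locking of 0.2, √(0.2² + 0.96/n) gives 0.223 at 100 breaths and 0.215 at 150, a rise of about 3%.

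**Artefact handling and cautious interpretation.** MaxFilter, head-position monitoring and ICA bear on movement and cardiac artefact, but they do not equalise events or cycle lengths. Avoiding causal claims does not help either: the descriptive statement that coupling differs between conditions would itself be wrong.

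**Conclusion.** The concern holds in a bounded form. The plan expects heart and breathing rate to differ between conditions and compares event-locked indices across those conditions, and nothing stated separates a rate effect from a coupling effect. It does not follow that a false coupling result is likely, or that it must favour slower breathing. The size turns on the index chosen and on rate differences that the article does not give.

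For a phase-locking index with no coupling and 30 participants, the false-positive rate runs from close to nominal for small heart-rate gaps to about 0.3 for a breathing gap of 5 per minute. These figures are for one uncorrected contrast; the omnibus-then-corrected procedure in 3.9.3 would give different values. The overlap figures show a direction of risk under an assumed response shape and are not estimates for this study. The primary outcomes are untouched. The point is worth acting on because coupling carries the mechanistic claim and the correction is inexpensive.

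**What to change.** In sections 3.7.4 and 3.9.1, state the following for the event-locked indices:

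1. Express each participant's index in each condition relative to a surrogate index from randomly shifted event times, using the same number of events in the same block. Alternatively, use equal event counts across the three conditions within each participant. Either removes the count bias, so both are not needed.
2. End the R-locked window before the next beat, or apply an overlap correction. Deleting beats with an early successor is not a good substitute, since it selects on heart rate.
3. Beside the main contrast, report a sensitivity analysis with condition-level heart rate and respiration rate as covariates.
4. Run the same condition contrast on the R-locked ECG and respiration-locked belt traces as a descriptive artefact check. It should not act as a veto: a non-significant contrast in 30 participants does not show absence of a difference, and a veto would block any coupling claim wherever physiology responds.

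If the preregistration already contains such controls, cite them here.

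The cost is wording, computing time and somewhat noisier indices. Equalising counts loses events: at 15 versus 10 breaths/min, 50 of 150 breaths, or one third, in the faster condition. Rate may itself be an effect of condition, so adjusting for it can remove part of a genuine effect; the adjusted and unadjusted results should therefore appear together.
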